### Concomitant medications

During the clinical trial participation period, the participant is advised not to take any medications other than the investigational product. However, if another medication is administered in combination at the investigator’s discretion, information regarding the medication (such as name, daily dose, administration period, and reason for administration) must be recorded in the case report form (CRF). Drug history is checked for all preceding/concurrent medications within four weeks based on the screening point.

The use of new medications that influence the results of a clinical trial during the administration period of an investigational product is prohibited. The use of emergency medications is not prohibited if a patient's asthma-related symptoms worsen temporarily. However, if a patient's asthma symptoms persistently worsen and additional medications such as systemic oral steroids, theophylline, other xanthine drugs, anti-IgE antibodies, and persistent anticholinergic bronchodilators are needed for continuous control, the clinical trial is halted and the relevant medication is administered. This is not applicable in cases where they are used momentarily for the short-term treatment of acute exacerbation of asthma.

### Outcome measurements

#### Primary outcome

##### Pulmonary function test (Forced Expiratory Volume in 1 s, FEV_1_)

Spirometry is a test that plays an essential role in the diagnosis and monitoring of asthma to identify airflow limitation [2]. Using spirometry, measurements of forced vital capacity (FVC), FEV_1_, among others are taken, and changes in FEV_1_% and liters are observed to measure the amount of change. The primary outcome of this study will be the average change in FEV_1_ scores between baseline and week 8.

#### Secondary outcomes

##### Pulmonary function tests (Peak Expiratory Flow, PEF; Forced Vital Capacity, FVC; Forced Expiratory Flow at 25–75%, FEF25–75)

Among the items tested by spirometry, PEF, FVC, and FEF25–75 are measured, and changes in % and liters are observed to measure the amount of change. PEF, FVC, and FEF25–75 will be evaluated at baseline and weeks 4 and 8.

##### Fractional exhaled nitric oxide (FeNO)

Fractional exhaled nitric oxide (FeNO) is a test utilized to ascertain the severity of bronchial inflammation, by measuring a substance known as nitric oxide present in the exhaled air [12]. The measurement is conducted by having the subject exhale at a constant rate for ~ 10 s into a mouthpiece connected to a monitor, thereby determining the concentration of nitric oxide. FeNO scores will be evaluated at baseline and weeks 4 and 8.

##### Asthma Control Test (ACT)

The Asthma Control Test (ACT) comprises five questions related to the frequency of asthma symptoms and the use of rescue medication over the past four weeks. Scores are interpreted as follows: 15 or below indicates a very poorly controlled condition, 16 to 19 indicates a poorly controlled condition, and 20 to 25 signifies a well-controlled condition [2]. The ACT will be evaluated at baseline and weeks 4 and 8.

##### Asthma Quality of Life Questionnaire (AQLQ)

The Asthma Quality of Life Questionnaire, AQLQ is a 32-item questionnaire used to assess the physical, occupational, emotional, and social characteristics of adults aged 17–70 with asthma [13]. The AQLQ is fully validated and effective in evaluating patients exhibiting mild to moderate asthma [14]. The AQLQ is composed of four domains: symptoms (12 items), activity limitations (6 general items and 5 patient-specific items), emotional function (5 items), and environmental stimuli (4 items). The AQLQ will be evaluated at baseline and weeks 4 and 8.

##### Questionnaire of asthma symptoms of Korean medicine 

The questionnaire on asthma symptoms in Korean medicine is evaluated at baseline and presented in a descriptive analysis.

**Deficiency and excess pattern identification questionnaire**

 The tool for assessing the deficiency and excess pattern identification of asthma patients used the questionnaire listed in the “Guideline for clinical trials with herbal medicinal products: antiasthmatic agents” presented by the Korea Food & Drug Administration [15]. This questionnaire was developed by modifying the deficiency and excess pattern identification items used in previous research, and the patient's asthma pattern is largely divided into deficiency and excess.

Excess patterns are divided into exogenous wind cold and excessive internal phlegm dampness, the latter subdividing into phlegm dampness, cold phlegm, and phlegm heat, and deficiency patterns are divided into lung deficiency, heart-kidney deficiency, and upper excess with lower deficiency, classifying asthma into seven pattern identifications. The total score for each pattern identification unit is 10 points for excess pattern and 11 points for deficiency pattern; only those with 5 points or more are recognized as pattern identifications. If there are two or more pattern identifications with five or more points, the one with the highest score is selected as the pattern identification. If the scores are the same, the pattern identification with greater weight is selected and classified.

**Cold-heat pattern questionnaire**

The asthma cold-heat pattern model of the patient used the Cold-Heat Pattern Questionnaire presented by Ryu et al. (2008) [16]. This questionnaire consists of 8 items on cold patterns and 7 items on heat patterns in six categories such as ‘thirst,’ ‘restlessness,’ ‘constipation,’ ‘chills,’ ‘cold hands and feet,’ and ‘diarrhea.’ The responses are measured using a 7-point Likert scale, which ranged from 'Not at all,’ ‘Not really,’ ‘Somewhat no,’ 'Neutral,’ 'Somewhat yes,’ ‘Yes,’ to 'Absolutely,’ based on the frequency and severity of the symptoms. The heat and cold scores are calculated as the sum of the averages of the weight categories. The heat and cold indices are calculated as percentages of the occupancy of the cold-heat attribute by dividing the heat and cold scores by the maximum heat and cold scores, respectively.

##### Serum IgE, eosinophil count, c-reactive protein (CRP)

Asthma is a disease characterized by chronic inflammation of the airways and is associated with elevated levels of blood eosinophils, immunoglobulin E (IgE), and inflammation-related indices such as CRP [17]. We plan to quantify these changes and assess their correlation with the disease progression. Serum IgE, eosinophil count, and CRP will be measured at baseline and weeks 4 and 8.

##### Frequency of rescue medicine

According to the Korean Asthma Management Guidelines (2015) [18], when symptoms of caution-level acute exacerbation occur, as presented in the asthma action plan during asthma patient management education, the emergency drug Ventolin Evohaler from GlaxoSmithKline is used, and its usage frequency is measured. The criteria presented at the caution level are as follows: 1. One or more symptoms, such as cough, wheezing, chest tightness, or shortness of breath are present. 2. Waking up at night because of asthma symptoms. 3. Interference with daily activities. 4. The peak expiratory flow rate is between 60–80% of the individual's maximum. In this case, symptom relievers (Ventolin Evohaler) are sprayed twice each, up to three times. The number of uses of the rescue medication will be evaluated at baseline and weeks 4 and 8. Additionally, assessments will be conducted via telephone visits at weeks 2 and 6.

### Safety assessment

Laboratory tests (liver function test, blood urea nitrogen (BUN), creatinine, eGFR, sodium, potassium, and chloride) and vital sign measurements will be conducted before drug administration and 4 and 8 weeks after administration. During the 2nd and 6th weeks of drug administration, adverse reactions will be checked via phone visits to evaluate any adverse reactions associated with the drug administration during the test period. If an adverse reaction occurs, a trial participation meeting will be held to estimate its association with the clinical drug.

To test the safety of the herbal medicine intake, AST, ALT, alkaline phosphatase (ALP), total bilirubin (TB), gamma glutamyl transferase (GGT), BUN, creatinine, and eGFR are measured. To check for damage to liver function caused by herbal medicine, AST, ALT, ALP, TB, and GGT levels are measured. This indicator was structured with reference to the herbal medicine-induced liver injury investigation forms to improve the research quality of herbal safety presented by Yoon et al. (2009) [19]. The presence of kidney function damage caused by herbal medicine intake is confirmed by BUN, creatinine, and eGFR.

Adverse events (AEs) refer to undesirable and unintended signs, symptoms, or diseases that occur during a clinical trial and do not necessarily have to be causally related to the treatment used in the clinical trial. Serious adverse events (SAEs) refer to medical situations that are of significance, including death, life-threatening situations, need for hospitalization or extension of hospitalization, permanent or severe disability and impairment, and congenital anomalies or abnormalities occurring in the fetus, among the AEs that occur in the clinical trial participants during the clinical trial.

Continuous AE monitoring is conducted for all participants throughout the trial period. If the person in charge of the clinical trial determines a clinically significant change through an objective examination, subjective symptom questioning, and blood tests, it is considered an AE. The researcher records all information related to the AE and SAE in the CRF, including the AE name, occurrence date, end date, intensity, correlation with the investigational drug, outcome, treatment status, and SAE status.

If an AE deemed to harm the participant is observed at any time during the clinical trial period, the researcher can temporarily suspend treatment. When the progression of the AE is tracked, its causal relationship with the treatment is assessed, and it is determined that the continuation of the treatment could harm the subject, the researcher will permanently discontinue the patient's participation in the clinical trial. The treatment in the clinical trial can be temporarily suspended or continued at the discretion of the researcher if the existing disease worsens during the clinical trial period. The clinical trial is immediately and permanently discontinued for all pregnant subjects. If any AE occurs that necessitates medical attention as determined by the investigator, appropriate action will be taken in accordance with the rules for compensating victims through insurance coverage.

### Statistical analysis

#### Effectiveness outcomes

Statistical analyses are conducted independently by a statistical expert using SAS. In the two-tailed tests, the level of significance is set at 0.05. All analyses primarily utilize intention-to-treat analysis, with per-protocol analysis conducted concurrently, and the results are presented together. In the demographic baseline data, continuous variables are presented as mean and standard deviation and are analyzed using an independent t-test or Mann–Whitney U test. Categorical variables are presented as frequency and proportion and analyzed using a chi-square test or Fisher's exact test (when the expected frequency is less than 5 in more than 25% of all values).

The primary efficacy evaluation is based on the mean change in FEV_1_ scores evaluated at week 8 (56 days post-dosing), whereas secondary efficacy evaluations compare the means of PEF, FVC, FEF25–75, FeNO, ACT scores, AQLQ scores, Serum IgE, eosinophil count, CRP, and the frequency of rescue medication use assessed at baseline and weeks 4 and 8. If the assumption of normality is satisfied, an independent t-test is conducted; otherwise, the Mann–Whitney U test is applied. However, if significant differences between the groups are found in baseline values, an analysis of covariance (ANCOVA) is performed. Missing data is replaced using the last observation carried forward method; each missing value is replaced with the participant's last observed value. For the secondary efficacy evaluation, the distribution of participants according to each diagnosis of Korean medicine pattern identification assessed at baseline is presented as frequency and proportion and visualized in tables or graphs through descriptive analysis.

Subgroup analysis will be performed according to the following criteria: First, subgroups will be divided according to the type of asthma medication (ICS or ICS + LABA) taken in addition to the LTRA at enrollment. Second, the effect will be further analyzed by age, separating younger patients (< 35 years) from older patients (> 60 years). Third, subgroups will be defined as male and female. Fourth, subgroups will be created based on severity as measured by ACT, ≤ 15 and > 15. Finally, subgroup analyses will be performed according to Korean medicine pattern identification.

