**Methods:**

This randomized, placebo-controlled, double-blind, parallel-group, multicenter study aims to evaluate the efficacy and safety of CSBHT as an additional treatment for patients with asthma, particularly for those with LTRAs. Overall, 198 participants will be randomly divided into intervention and control groups, with the former receiving CSBHT thrice daily and the latter receiving a placebo. Follow-ups at weeks 0, 4, and 8 will include outcome measurements, medication dispensation, and adverse reaction monitoring. The primary outcome is the mean change in forced expiratory volume in one-second scores, with secondary outcomes including changes in peak expiratory flow, forced vital capacity, forced expiratory flow 25–75%, fractional exhaled nitric oxide, Asthma Control Test, Asthma Quality of Life Questionnaire, serum IgE, eosinophil count, C-reactive protein, rescue medication usage, and a descriptive analysis of the questionnaire on asthma symptoms in Korean medicine. Safety assessments will be conducted using laboratory tests, vital signs, and monitoring of adverse events. Economic evaluations will be conducted using either cost-minimization analysis or cost-utility analysis.

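### Secondary outcomes are declared as changes, but the analysis text compares means at visits and adjusts for baseline only after a significant baseline test; the variable needs reconciling and baseline should always be a covariate

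*Protocol article*

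**What the plan says.** The abstract (Methods) declares the secondary outcomes as changes: "with secondary outcomes including changes in peak expiratory flow, forced vital capacity", followed by the remaining measures. Two outcome sections agree. For PEF, FVC and FEF25–75, "changes in % and liters are observed to measure the amount of change". For serum IgE, eosinophils and CRP, "We plan to quantify these changes and assess their correlation with the disease progression". The sections on FeNO, ACT, AQLQ and rescue medication say only that these are evaluated at baseline, week 4 and week 8.

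The Effectiveness outcomes section treats primary and secondary outcomes differently. "The primary efficacy evaluation is based on the mean change in FEV_1_ scores evaluated at week 8", "whereas secondary efficacy evaluations compare the means of PEF, FVC" and the other measures, assessed at baseline and the two later visits. The test is then fixed: "If the assumption of normality is satisfied, an independent t-test is conducted; otherwise, the Mann–Whitney U test is applied". Baseline enters by one route only: "if significant differences between the groups are found in baseline values, an analysis of covariance (ANCOVA) is performed".

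**The concern.** A level at a visit and a change from baseline are different analysis variables. They have different variances and can give different p-values from the same data. The protocol declares one and, on the plain reading, tests the other. All ten tested secondary outcomes are affected: PEF, FVC, FEF25–75, FeNO, ACT, AQLQ, IgE, eosinophils, CRP and rescue use. With both versions in print, the variable could be settled after results are known.

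The baseline rule adds to this. Adjustment depends on a significance test of baseline values. In a randomised trial that test fires by chance in about 5% of comparisons, whether or not the baseline is prognostic. In the rest, the precision that a prognostic baseline offers is not used, and a moderate chance imbalance stays in the comparison.

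**Working it through.** **The plan's own figure.** The Sample size section gives an effect size of 0.437, two-sided alpha 0.05, power 0.80 and 1:1 allocation. A two-sample t-test needs 84 per arm, total 168 (the normal approximation gives 83 per arm). Allowing for dropout, 168/0.85 = 197.6, so 198. Both figures reproduce. They concern change in FEV1; no power is stated for any secondary outcome.

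**Inputs for the check.** From the plan: 84 per arm and two-sided 0.05. Assumed, because the documents give neither: a true week-8 difference of 0.3 between-patient SD, and a baseline-to-week-8 correlation r from 0 to 0.9. Also assumed: equal SDs at both visits and roughly normal outcomes.

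**Imbalance left unadjusted.** The standard error of a baseline difference is √(2/84) = 0.154 SD. It is non-significant up to 1.96 × 0.154 = 0.30 SD. (With all 198 analysed, 1.96 × √(2/99) = 0.28 SD.) Given a baseline imbalance b, the expected shift in the unadjusted week-8 difference is r·b for levels and −(1 − r)·b for change. With b = 0.30:

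- r = 0.8: levels 0.8 × 0.30 = +0.24 SD; change −0.2 × 0.30 = −0.06 SD.
- r = 0.3: levels +0.09 SD; change −0.7 × 0.30 = −0.21 SD.

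Neither unadjusted variable is protected at every r. Under the normal model, adjustment for baseline removes the shift.

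**Power.** Power = Φ(0.3/√(2v/84) − 1.96), with v = 1 for levels, 2(1 − r) for change and 1 − r² for ANCOVA on baseline. Worked case, r = 0.8:

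- levels: 0.3/0.1543 = 1.944; Φ(−0.016) = 49%
- change: v = 0.40, 0.3/0.0976 = 3.074; Φ(1.114) = 87%
- ANCOVA: v = 0.36, 0.3/0.0926 = 3.240; Φ(1.280) = 90%

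| r (assumed) | Levels | Change | ANCOVA |
|---|---|---|---|
| 0 | 49% | 28% | 49% |
| 0.3 | 49% | 38% | 53% |
| 0.5 | 49% | 49% | 61% |
| 0.7 | 49% | 71% | 78% |
| 0.8 | 49% | 87% | 90% |
| 0.9 | 49% | 99% | 99% |

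A noncentral-t calculation agrees within about one percentage point. For a smaller assumed effect of 0.2 SD it gives 25% on levels at any r; change has 15%, 25% and 53% at r = 0, 0.5 and 0.8, and ANCOVA 25%, 32% and 57%.

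**Break-even.** With equal SDs, change beats levels when 2(1 − r) < 1, that is r > 0.5. ANCOVA is at least as precise as both at every r, since 1 − r² ≤ 1 and 1 − r² = (1 − r)(1 + r) ≤ 2(1 − r); the one degree of freedom spent is negligible here.

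**The plan's only correlation.** The Sample size section assumes r = 0, for FEV1. With the Table 2 SDs (pooled 0.276 before and 0.775 after treatment) and a 0.36 L difference (0.84 − 0.48, taking the control change as 1.37 − 0.89), levels have 85% power at r = 0 and change 80%. Break-even there is r = 0.276/(2 × 0.775) = 0.18. Which unadjusted variable wins thus depends on quantities that the plan does not give for the secondary outcomes.

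**The case against.** **The wording is condensed.** The section never says that the means are raw, and the sentence could be shorthand for mean changes between the listed visits. That stands as far as it goes: visit levels are the plain reading, not an explicit statement. But the contrast with the primary mean change points to levels, and if change was meant the sentence still needs correcting. An unseen analysis plan does not remove the conflict, because this document states the variable, the visits and the tests itself.

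**The conflict is uneven.** For FeNO, ACT, AQLQ and rescue use, change rests on the abstract's list alone. This stands.

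**A reader might infer that the trial tests a different treatment effect from the one declared.** The documents do not support that. Under randomisation, levels and changes have the same expected between-arm difference.

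**A reader might infer that much power is lost, above all for spirometry.** That would need a high baseline correlation. The documents give none for any secondary outcome, and at their one stated value (r = 0, for FEV1) levels do better than change.

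**A reader might infer that every baseline imbalance passes into the result, or that the baseline comparison has no purpose.** The ANCOVA rule contradicts both: a significant imbalance is adjusted for, and the baseline comparison is its trigger. Only imbalance short of significance is left.

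**Matching the declared outcome needs only the word change.** True for the wording alone. It would leave the conditional ANCOVA in place, and below r = 0.5 with equal SDs it would lower power relative to levels.

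**Conclusion.** The point holds as a conflict of wording together with a weak baseline rule. The abstract, and the outcome sections for spirometry and blood markers, declare changes; the analysis section on its plain reading compares visit levels. Baseline is used only when a significance test fires, which leaves imbalances of up to about 0.30 SD unadjusted at 84 per arm.

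The consequences are reduced precision, sensitivity to chance imbalance and an analysis choice left open. For an assumed 0.3 SD effect, always adjusting for baseline moves power from 49% on levels to 53% at r = 0.3, 61% at 0.5, 78% at 0.7 and 90% at 0.8, with no gain at r = 0. These figures rest on assumed correlations, equal SDs and approximate normality. They need not carry over to skewed markers or rescue-use counts, which the plan may send to the Mann–Whitney test. The definition of the primary outcome and the sample size are not affected. The change should be made, but the trial's main conclusion does not depend on it.

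**What to change.** In the Effectiveness outcomes section, replace the comparison of means across the three visits. For each continuous secondary outcome, specify the between-arm difference in change from baseline to week 4 and to week 8, estimated with the baseline value always as covariate. Use a transformation or a rank-based equivalent for skewed outcomes. Drop the baseline significance test as the trigger for adjustment, and present baseline means descriptively only.

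This aligns the analysis with the abstract and the outcome sections. It also ends the choice between level and change: with baseline in the linear model, both give the same treatment estimate and p-value. The cost is a few sentences, to be settled before unblinding. The protocol already schedules the baseline values, so no new data are needed.

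### Carrying the last rescue-inhaler count forward assigns use, or non-use, to time when the patient was not observed, and can bias the comparison either way

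*Protocol article*

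**What the plan says.** The protocol article, under Frequency of rescue medicine, defines the outcome as a count: "The number of uses of the rescue medication will be evaluated at baseline and weeks 4 and 8". It adds that "assessments will be conducted via telephone visits at weeks 2 and 6". It does not state the period that each count covers, or whether the telephone counts overlap the visit counts.

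Under Effectiveness outcomes, "the frequency of rescue medication use assessed at baseline and weeks 4 and 8" stands in one list with lung function, FeNO, questionnaire scores and laboratory values, all compared by means. One test rule covers the list: "If the assumption of normality is satisfied, an independent t-test is conducted; otherwise, the Mann–Whitney U test is applied". An exception follows: "if significant differences between the groups are found in baseline values, an analysis of covariance (ANCOVA) is performed". One missing-data rule also covers it: "Missing data is replaced using the last observation carried forward method". No observation time or rate is mentioned. Intention-to-treat and per-protocol results are to be shown together.

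**The concern.** LOCF treats a value as a state that persists until the next measurement. A count is different: it is what happened in one interval. Copying it into a later interval creates events, or an absence of events, that nobody recorded. The problem is sharpest for patients who leave before week 4. On the visits listed for analysis, their only value is the baseline count, so pre-treatment use is scored as on-treatment use at both later visits. If the week 2 telephone count were taken as the last value instead, a count over a possibly shorter period would fill the later visits.

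Leaving is unlikely to be unrelated to rescue use. Under Concomitant medications, participation ends when asthma keeps worsening and further continuous treatment is needed. Withdrawal criteria adds low compliance, a changed LTRA prescription and adverse reactions. The carried count may therefore be too high or too low, and the number of carried counts may differ between arms. At stake is the trial's direct count of reliever use, and whether a difference between groups reflects treatment or who left.

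**Working it through.** **Inputs from the protocol article.** 168 evaluable, 15% dropout and 198 randomised (Sample size); eight weeks of treatment (Drug interventions); counts at baseline and weeks 4 and 8 (Frequency of rescue medicine). The planned total reproduces: 168 / (1 − 0.15) = 197.6, rounded up to 198. No rescue rate, dispersion, share of non-users or expected effect is given, so everything from step 2 on rests on assumptions.

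**1. How much would be imputed.** Leavers: 198 × 0.15 = 29.7, about 30. Total follow-up: 198 × 8 = 1,584 patient-weeks.

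- All leave after week 4: 30 × 1 = 30 visit values, at most 30 × 4 = 120 patient-weeks (7.6%).
- All leave before week 4: 30 × 2 = 60 visit values, at most 30 × 8 = 240 patient-weeks (15.2%).

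**2. Dropout equal in both arms and unrelated to use.** Assume a constant true rate ratio of 0.60 and half the leavers (7.5% of each arm) gone before week 4. Their baseline counts carry no treatment effect, so the week 8 ratio of means is 0.925 × 0.60 + 0.075 × 1.00 = 0.63. In simulations (99 per arm, negative binomial counts, mean 1, 4 or 10 per four weeks, dispersion 0.5 to 2) it averaged 0.63 to 0.66. Averaging ratios pushes this up a little: the null runs averaged 1.00 to 1.03. Type I error of the planned tests stayed at 0.03 to 0.06. Here LOCF only dilutes the effect.

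**3. Dropout unequal and related to use.** Let the carried count be f times the true average, with true rates equal in both arms. With dropout fractions d_T and d_C, the apparent ratio is [(1 − d_T) + d_T·f] / [(1 − d_C) + d_C·f].

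| f | d_C | d_T | Apparent ratio (true 1.00) |
|---|---|---|---|
| 2 | 0.20 | 0.10 | 1.10 / 1.20 = 0.92 |
| 3 | 0.20 | 0.10 | 1.20 / 1.40 = 0.86 |
| 2 | 0.10 | 0.20 | 1.20 / 1.10 = 1.09 |
| 3 | 0.10 | 0.20 | 1.40 / 1.20 = 1.17 |
| 2 or 3 | 0.15 | 0.15 | 1.00 |

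If the carried counts are too low (f < 1, for example zeros), each direction reverses.

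**4. Does a count model gain power?** Simulated, 99 per arm, two-sided 0.05.

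- Negative binomial counts, one four-week interval, no dropout, rate ratio 0.6: Mann–Whitney was about 2 to 19 points below the negative binomial test; the t-test was within 4.5 points of it.
- Same type of counts, mean 4, dispersion 1, 15% dropout: Mann–Whitney with LOCF 0.70, t-test with LOCF 0.81, negative binomial on weeks 4 to 8 without LOCF 0.86, negative binomial on all observed time 0.95, Mann–Whitney on the observed rate 0.83.
- Treatment lowers the share of users (50% to 30%, or 70% to 50%) and amounts are heavy-tailed, no dropout: Mann–Whitney 0.75 to 0.77, negative binomial 0.34 to 0.39. In the heaviest-tailed null, negative binomial type I error with model-based inference was 0.195. With robust errors it was still about 0.08 to 0.13 in the zero-heavy nulls tried.

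The sign of the power difference therefore depends on a count distribution that the documents do not describe.

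**The case against.** Mann–Whitney is a valid test for skewed, tied counts, and the planned rule adds ANCOVA when baseline differs. LOCF is the article's general rule for efficacy data, so rescue use is not singled out. With equal dropout unrelated to use, LOCF left type I error near 5%. The article condenses a fuller document, and how the telephone data are combined may be settled there. Reliever use also enters through the Asthma Control Test.

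Most of this stands. The choice of Mann–Whitney or t-test is not an error, and the article's silence on combining telephone counts is not a finding. Simply adding telephone to visit counts could count the same use twice. What does not answer the point is that LOCF is general: the article does state it for a list that includes this outcome, and it fits an interval count particularly badly. Nor does the conditional ANCOVA help, since it adjusts for baseline without removing invented follow-up values.

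A reader might infer more: that the planned tests are weak here, that a negative binomial model would gain a known amount of power, or that LOCF inflates use. The documents support none of these. They give no rate, dispersion or effect; the power ranking reverses under plausible data; and LOCF carries zeros as readily as uses.

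**Conclusion.** The point holds for the missing-data rule. Carrying rescue counts forward fills unobserved time with earlier counts for about 30 of 198 patients if the planned dropout occurs, and for those who leave before week 4 it scores pre-treatment use as treatment response. The size of the bias is unknown. It is mild dilution (0.60 to about 0.63) if leaving is unrelated to use. It ranges from about 0.86 to 1.17 around a true 1.00 if dropout is 20% against 10% and carried counts are two to three times the true average. Those dropout and use figures are assumptions. Any power gain from another model also depends on the unknown count distribution. The outcome is secondary and the sample size rests on FEV₁ alone, so this is a worthwhile improvement that leaves the primary conclusion untouched.

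**What to change.** Change the analysis wording for rescue use only:

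- Do not apply LOCF to rescue counts.
- Analyse observed uses from week 0 to last contact relative to observed time, adjusted for baseline use whether or not baseline differs significantly.
- Report a rate ratio with 95% CI from a count model with log observed time as offset and robust or permutation-based inference. Permutation is the safer choice if the data are zero-heavy with a long tail, because robust errors alone did not hold 5% in such nulls.
- Prespecify Mann–Whitney on the observed rate as a sensitivity analysis.
- Use the week 2 and week 6 telephone counts to establish use and time for early leavers. State the period that each count covers, and count each period once.

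The rate then describes use while observed. If leaving follows worsening, that is still a selective picture, so a missing-data sensitivity analysis is advisable.

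Cost: slightly more analysis work and a power trade-off that depends on the distribution. No extra patients, visits or measurements are needed.
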